### Primary outcome

2.7

The main outcome is the change in percent predicted VO2_max_ measured during CPET, between baseline (M0) and 12-month follow-up (M12) (see Table 2).

**Table 2 t0010:** Outcome measures.

Primary outcome
• Maximum oxygen uptake (VO2_max_)

Secondary outcomes
• Quality of life score: PedsQL self-questionnaire (version 13–18 years for adolescents and version 18–25 years for young adults)
• Proxy version of the PedsQL for parents of adolescents (aged 13–18 years old)
• Level of anxiety (STAI self-questionnaire for young adults and the STAI-Children self-questionnaire for adolescents)
• Level of depression (BDI self-questionnaire for young adults and CDI self-questionnaire for adolescents)
• Other cardiopulmonary exercise tests parameters o Ventilatory anaerobic threshold (VAT) o Ventilatory efficiency (VE/VCO2 slope) o Oxygen uptake efficiency slope (OUES) o Oxygen pulse o Respiratory response to hypercapnia using the rebreathing technique with inhaled CO2 and measuring P0.1 at rest
• Clinical outcomes: NYHA functional class, blood pressure, healthcare usage (primary and secondary care contacts, hospitalisation), and medication
• The socio-economic status of the patient and/or the family (only at baseline)
• Safety outcomes
• Acceptability of the intervention to participants

### Secondary outcomes

2.8

The following outcomes will be measured at baseline (M0) and 12-month follow-up (M12) (see Table 2):•The PedsQL self-reported HRQoL score. Two versions of the PedsQL questionnaire (13–18 and 18–25 years old) will be used for adolescents and young adults, respectively [34].•The level of anxiety with the self-administered State and Trait Anxiety Inventory (STAI) questionnaire for young adults and the STAI-Children questionnaire for adolescents [35].•The level of depression with the self-administered Beck Depression Inventory (BDI) questionnaire for young adults and the Child Depression Inventory (CDI) questionnaire for adolescents [36].•The level of physical activity with the Ricci and Gagnon questionnaire, composed of 8 items (total score of 16 points: no activity; 17–32 points: moderate activity; 33–40 points: intensive activity) [37].•The clinical outcomes: NYHA functional class, blood pressure, body mass index (BMI), healthcare usage (primary and secondary care contacts, hospitalisation), cardiac events, and medication.•Other CPET variables: the ventilatory anaerobic threshold (VAT), the ventilatory efficiency (VE/VCO2 slope), the oxygen uptake efficiency slope (OUES), the oxygen pulse (VO2/HR), and the pulse oximetry (SpO2), will be collected, using the same method as in our previous CPET studies [18].•Respiratory response to hypercapnia using the rebreathing technique with inhaled CO2 and measuring P0.1 at rest [38].

### Statistical analysis

2.9

A comparative analysis of the baseline characteristics of randomised subjects between the two arms in the study will be performed by giving the frequencies of the different categories for the qualitative variables, and the mean with standard deviation for quantitative variables. Our main analysis will be an intention-to-treat analysis, in which each randomised subject will be analysed in his/her treatment arm. The evolution of the percent predicted VO2_max_ between inclusion (V0) and visit at 12 months (V1) will be compared between the groups using a Student test.

A secondary per-protocol analysis, including all randomised subjects with a valid primary efficacy measurement and with no important protocol deviation (patients who have successfully completed the Sophrology program, with at least 80% of the sessions), will also be carried out to study mechanisms of action. In case of non-comparability of the groups on one of the baseline characteristics, an adjustment will be considered. Analyses will be performed using SAS statistical software (version 9.4; SAS Inc, Cary, North Carolina) using a 5% bilateral alpha risk.

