### Study design

2.1

The SOPHROCARE trial is a prospective, multicentre, randomised, controlled, parallel arm study, with a 12-month follow-up. Participants will be randomly allocated in a 1:1 ratio to either intervention or control group arms, with minimization on centre of inclusion and age groups (13–17 years old vs 18–25 years old). Randomisation numbers will be computer generated and assigned in strict sequence, using a secure, web-based randomisation system (CS RANDOM module, Clinsight Software). Randomisation will be managed by the Clinical Research Unit of Montpellier University Hospital, France, independently from the investigators. All screened subjects will be identifiable throughout the study by a unique subject number.

Eligible patients will be randomised into 2 groups (Fig. 1):•Group 1: intervention group, e.g., patients participating in the Sophrology program in addition to their usual clinical follow-up.•Group 2: control group, e.g., patients will have a regular non-modified clinical follow-up with no Sophrology intervention during the 12-month study period. However, they will be able to participate in the Sophrology program if they wish, once the 12-month study period is over.

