### Setting

2.2

Overall, 5 CHD centres in France will participate in the study (Montpellier University Hospital, Palavas Saint-Pierre Institute, Toulouse University Hospital, Paris Necker Sick Children University Hospital, Bordeaux University Hospital). Patients will be recruited in tertiary care public institutions, and university centres labelled by health authorities as referral centres for complex congenital heart diseases (M3C national health network). The study will be led by a local principal investigator (supported, when necessary, by a co-investigator), a research nurse or fellow, two sophrologists, and a clinical research assistant, all of whom are trained in Good Clinical Practice and in the requirements of the study protocol. Each site will be responsible for the recruitment and scheduled follow-up visits of participants.

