### Sample size

2.6

A total of 188 patients need to be recruited (94 intervention: 94 control). The primary outcome is the change in percent predicted maximum oxygen uptake (VO2_max_) between baseline (M0) and 12-month follow-up (M12). The mean VO2_max_ from our own cohort of young patients with CHD is 39.4 ± 8.9 ml/kg/min [6]. In the meta-analysis from Gomes-Neto et al., cardiac rehabilitation increases the VO2_max_ by an average of 13% in young CHD patients [30]. In the SOPHROCARE trial, we hypothesized to observe a VO2_max_ increase of 10% in the Sophrology group. Therefore, with an expected difference of 10%, an 80% power, a bilateral alpha risk of 5%, and potentially 20% of loss to follow-up and/or missing data on the primary outcome, we need to include 78 patients in each group. When considering 20% of loss to follow-up and/or missing data on the primary outcome, we need to include 94 patients in the group 1 and 94 patients in the group 2.

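### The primary Student test on change conditions on neither baseline VO2max nor the minimisation factors; it is valid, but less precise than a pre-specified ANCOVA on the same data

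*Protocol article*

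**What the plan says.** Section 2.9 (Statistical analysis) of the protocol article makes intention-to-treat the main analysis. The evolution of percent predicted VO2max from inclusion to 12 months "will be compared between the groups using a Student test". No covariate is named.

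Section 2.1 (Study design) sets 1:1 allocation "with minimization on centre of inclusion and age groups", with age split into 13–17 and 18–25 years. Section 2.2 (Setting) lists five centres.

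The only mention of adjustment is in the second paragraph of section 2.9, after the per-protocol analysis: "In case of non-comparability of the groups on one of the baseline characteristics, an adjustment will be considered".

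Section 2.6 (Sample size) plans an unadjusted comparison of two means. Its only variability figure is this: "The mean VO2_max_ from our own cohort of young patients with CHD is 39.4 ± 8.9 ml/kg/min".

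**The concern.** Baseline percent predicted VO2max is part of the outcome definition, so every analysable patient has it. Allocation is deliberately balanced on two further variables. The stated test makes limited use of the first and none of the other two.

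The change score subtracts baseline with a slope of exactly 1. If the true slope is lower, as regression to the mean implies, a chance baseline difference d between the arms is over-corrected. With equal SDs at both visits, the change-score difference carries an expected error of −(1−r)d given that imbalance, where r is the baseline to 12-month correlation.

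Leaving out the minimisation factors has a different effect. Minimisation reduces the true variability of the treatment difference, but the t test's standard error does not reflect this, so the test is conservative to the extent that those factors predict change.

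The adjustment sentence does not settle the matter. It gives no criterion for non-comparability, names no covariate and commits only to considering an adjustment. Its place beside the per-protocol text leaves unclear whether it applies to the primary analysis. It also lets the model be chosen after the data are seen. Centre and age group are balanced by design, so they are the variables least likely to trigger it.

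At stake are the width of the primary confidence interval, the power, and the certainty that one model was fixed in advance.

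**Working it through.** **Inputs from section 2.6.** Mean 39.4 and SD 8.9 ml/kg/min; expected difference 10%, so 0.10 × 39.4 = 3.94; 80% power; two-sided 5%; 78 per group, raised to 94 for 20% loss. Evaluable per arm: 94 × 0.8 = 75.2, about 75. **Assumed, not in the article:** r, and the share of outcome variance explained by centre and age group.

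**The plan's own figure.** n per group = 2[8.9 × (1.960 + 0.842)/difference]². With the difference rounded to 4.0 this is 77.7, so 78, which reproduces the plan. With 3.94 it is 80.1, so 81. The calculation has no correlation term, and 94 is 78 × 1.2 = 93.6 rounded up.

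**Variance comparison.** With the same SD s at both visits:

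- change score: 2(1−r)s²
- ANCOVA: (1−r²)s²
- ratio, ANCOVA to change score: (1+r)/2

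The ratio is 0.75, 0.85 and 0.90 at r = 0.5, 0.7 and 0.8. To match ANCOVA, the t test would need 1/0.75 = 1.33, 1/0.85 = 1.18 or 1/0.90 = 1.11 times the patients. The direction does not need equal SDs. With SDs s0 and s1, change-score variance minus ANCOVA variance is (s0 − r·s1)², which is never negative.

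**Illustrative power.** Power = Φ(3.94/[SD × √(2/75)] − 1.96). The article does not say whether 8.9 stands for the SD of level or of change in the calculation, so both readings are shown.

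| r | 8.9 = SD of level: t test | ANCOVA | 8.9 = SD of change: t test | ANCOVA |
|---|---|---|---|---|
| 0.5 | 77% | 88% | 77% | 88% |
| 0.7 | 94% | 97% | 77% | 84% |
| 0.8 | 99.0% | 99.5% | 77% | 82% |

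Example at r = 0.5: the SD of change is 8.9 × √(2 × 0.5) = 8.9, giving Φ(2.71 − 1.96) = 77%. The ANCOVA SD is 8.9 × √0.75 = 7.71, giving Φ(3.13 − 1.96) = 88%. The two readings coincide at this r.

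**Minimisation factors.** This was simulated with 150 patients, five centres by two age groups, minimisation with an assumed 80% biased coin, and 3,000 runs (Monte Carlo error √(0.05 × 0.95/3000) = 0.4 percentage points).

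| Outcome variance explained by centre and age group (assumed) | True alpha, unadjusted t test | True alpha, adjusted for both factors |
|---|---|---|
| 0% | 5.1% | 5.1% |
| 5% | 4.3% | 4.9% |
| 10% | 3.8% | 4.9% |

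As a check at 10%, under perfect balance: 2[1 − Φ(1.96/√0.90)] = 3.9%.

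**The case against.** The plan is coherent on this point: the outcome is defined as a change, the sample size compares unadjusted means, and the test does the same. Under randomisation the t test on change is unbiased, and omitting the minimisation factors makes it conservative. A reader might infer that the primary analysis is invalid or risks false positives. The article does not support that.

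A reader might also say that the test ignores baseline. It does not: baseline is subtracted, though not conditioned on. Nor can the plan be said to be silent on imbalance, since section 2.9 contemplates adjustment. That provision counts in its favour, but it is not a pre-specified model.

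The size of the gain is open to real dispute. The article gives no r, and if 8.9 is the SD of level the power gain is about 3 points at r = 0.7 and half a point at r = 0.8. The inputs are in ml/kg/min while the endpoint is in percent predicted, so no power figure here describes the endpoint itself. Section 2.7 harmonises the exercise tests, centralises the calculations and normalises to reference values, which may leave centre and age group little to explain.

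These points limit the magnitude. They do not reverse the direction: apart from a few degrees of freedom, the adjusted analysis is at least as precise.

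**Conclusion.** The point holds as one of efficiency and pre-specification. The article itself fixes the test, so this is not a detail left to an unseen analysis plan.

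The variance ratio (1+r)/2 is free of units and rests only on equal SDs and the assumed r. For r from 0.5 to 0.8, the t test gives up precision worth 11% to 33% more patients. In power, using the sample-size inputs as an illustration, the gain from ANCOVA runs from about half a point to about 11 points, depending on r and on what 8.9 measures. The 11-point gain at r = 0.5 is the top of the range shown and should not be quoted alone. It would also go too far to conclude that the trial is underpowered because of this test: if 8.9 is the SD of level and r is 0.7 or more, power with the t test already exceeds 90%.

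The conservatism is conditional too: true alpha is about 5%, 4.3% and 3.8% if centre and age group explain 0%, 5% and 10% of the variance.

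**What to change.** Before database lock, name as the primary analysis a linear model of 12-month percent predicted VO2max on arm, baseline percent predicted VO2max, centre and age group (13–17 or 18–25 years). Report the adjusted mean difference with its 95% confidence interval. Using change as the response in the same model gives the identical treatment estimate, so the outcome definition can stay as it is.

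Let this model replace the sentence on adjustment in case of non-comparability, so that two adjustment rules do not stand side by side. Keep the Student test on change as a sensitivity analysis.

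The cost is a sentence or two in section 2.9 and in any analysis plan. No new data are needed. With 150 evaluable patients, the residual degrees of freedom fall from 150 − 2 = 148 to 150 − 8 = 142 (intercept, arm, baseline, four centre terms, one age term), a negligible loss.

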### Study population

2.4

Patients with a CHD, as defined by the international ACC-CHD classification [28] and aged from 13 to 25 years old, will be prospectively and consecutively recruited in the participating centres, during an outpatient visit. Patients with a recent (<3 months) medical check-up including a cardiology consultation, an ECG, an echocardiography, and a cardio-pulmonary exercise test (CPET), as detailed in the current European guidelines [29], will be screened (see Table 1).

**Table 1 t0005:** Trial entry.

Inclusion criteria
• Male or female aged 13–25 years old
• Patients with a congenital heart disease (CHD), as defined by the international ACC-CHD classification
• Written informed consent for adult patients, or legal guardians for minors

Exclusion criteria
• Absolute contraindication for cardio pulmonary exercise test
• Cardiac surgery or cardiac catheterization planned during the 12-month study period
• Pregnancy in female patients
• Patient undergoing cardiac rehabilitation during the 12-month study period
• Severe intellectual disability with inability to understand the study procedures and/or the quality of life questionnaire
• Expected difficulty to fully participate to the Sophrology program
• Participation in an interventional research during the 12-month study period

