### Intervention

2.5

The SOPHROCARE trial includes a Sophrology program divided into 8 group sessions of 1 h each. All participating centres will use the same program, under the supervision of one of three trained sophrologists ([name]), as in our previous similar study [19]. Each group session will be delivered in-person by one of the sophrologists and involve 5 ± 2 patients.

The first part of the session, lasting about 15 min, will start with a discussion (“pre-sophronic dialogue”), in order to create a climate of confidence, including a brief presentation of sophrology. Patients will be asked about their desires, interests and activities. Then the main part of the session, of approximately 30 min, will lead the patient to a level between awakening and sleep (“sophroliminal level”), using a slow and monotone-directed speech. Patients’ state of relaxation should facilitate “letting go,” focusing on body sensations, and improving their well-being (“sophronisation of vital base”). The techniques will be adapted to patients’ age, availability, and energy. The session will end with a final discussion (“post-sophronic dialogue”), putting into words the different sensations felt without any judgment or interpretation (“pheno-description”).

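### The secondary per-protocol analysis selects on session attendance in the intervention arm only, so it loses the protection of randomisation and cannot show mechanism

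*Protocol article*

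**What the plan says.** Section 2.9 (Statistical analysis) puts intention-to-treat first: "Our main analysis will be an intention-to-treat analysis, in which each randomised subject will be analysed in his/her treatment arm". It then adds a secondary per-protocol analysis "including all randomised subjects with a valid primary efficacy measurement and with no important protocol deviation". The only content given for the absence of a deviation is a parenthesis: "patients who have successfully completed the Sophrology program, with at least 80% of the sessions". The purpose is stated in the same sentence: the analysis "will also be carried out to study mechanisms of action". On adjustment, the section says: "In case of non-comparability of the groups on one of the baseline characteristics, an adjustment will be considered".

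Section 2.5 (Intervention) describes "a Sophrology program divided into 8 group sessions of 1 h each". Section 2.1 (Study design) says of the control group: "patients will have a regular non-modified clinical follow-up with no Sophrology intervention during the 12-month study period". Table 1 excludes, before randomisation and in both arms, patients with "Expected difficulty to fully participate to the Sophrology program".

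**The concern.** Attendance happens after randomisation and is the patient's own choice. Selecting on it in one arm leaves attenders on one side and, on the other, a mixture of patients who would have attended and patients who would not. Any difference between those two types of patient then enters the estimated effect.

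The article itself describes a route for such a difference. The Introduction reports that young patients with CHD have limited motivation for structured hospital-based programmes, so completing eight sessions marks a motivated subgroup. The outcome depends on effort: two of the four criteria for a maximal test in section 2.7 are the patient's tolerance limit and failure to keep up the pedalling rate despite encouragement. Motivation could therefore raise both attendance and the 12-month result without any effect of Sophrology.

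The stated purpose is a second difficulty. Restricting the VO2max comparison to completers is an analysis of adherence. It measures no intermediate step and cannot tell one mechanism from another.

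**Working it through.** The plan gives no figure for this point, so there is nothing to reproduce. The check has two parts.

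**1. Which arm the rule can act on.** The criterion (section 2.9) is a share of sessions attended. Controls have no sessions (section 2.1), so the attendance criterion can remove patients only from the intervention arm. With 8 sessions, 0.80 × 8 = 6.4, so the rule means at least 7 of 8 (87.5%), and 6 of 8 (75%) does not qualify.

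**2. How large the selection could be.** This is an illustration with no true effect.

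Inputs from the article: 94 patients per arm and 20% loss (section 2.6), which gives 94 × 0.8 ≈ 75 evaluable per arm; two-sided alpha 5%.

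Assumed, because the article gives neither: the share *a* of the intervention arm that attends enough sessions, and the correlation *r* between a normal latent propensity to attend and the change in the outcome. Attenders are the top fraction *a*. Controls are not selected on attendance. The outcome is in SD units.

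- Cut-off: c = Φ⁻¹(1 − a); λ = φ(c)/a
- Spurious benefit: b = r × λ
- Variance among attenders: v = 1 − r² λ(λ − c)
- Standard error: SE = √(v/(75a) + 1/75)
- Type I error: 1 − Φ(1.96 − b/SE) + Φ(−1.96 − b/SE)

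Worked case, a = 0.70 and r = 0.2: c = −0.524; λ = 0.348/0.70 = 0.497; b = 0.2 × 0.497 = 0.099; v = 1 − 0.04 × 0.497 × 1.021 = 0.980; SE = √(0.980/52.5 + 1/75) = 0.179; b/SE = 0.555; type I error = 0.080 + 0.006 = 0.086.

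| Share attending | λ | Bias in SD, r = 0.2 | Bias in SD, r = 0.3 | Type I error, r = 0.2 | Type I error, r = 0.3 |
|---|---|---|---|---|---|
| 90% | 0.195 | 0.04 | 0.06 | 5.6% | 6.4% |
| 80% | 0.350 | 0.07 | 0.10 | 6.9% | 9.4% |
| 70% | 0.497 | 0.10 | 0.15 | 8.6% | 13.4% |
| 60% | 0.644 | 0.13 | 0.19 | 10.6% | 18.1% |

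Over r = 0.1 to 0.5, the type I error runs from 5.2% (90% attending, r = 0.1) to 43% (60% attending, r = 0.5).

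The bias is left in SD units. The SD of 8.9 ml/kg/min in section 2.6 is the spread of absolute VO2max in a cohort at one time. The outcome analysed is change in percent predicted VO2max, whose SD the article does not give.

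**The case against.** The strongest reply is that a per-protocol analysis beside intention-to-treat is common practice and that the article labels it secondary. Nothing in section 2.9 lets it support an efficacy claim. That stands: the error rates above belong to this one analysis and not to the trial's main test.

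The second reply is that the size is assumed. That also stands. At 90% adherence the effect is close to negligible, and the Table 1 exclusion for expected difficulty in participating makes higher adherence more likely. Because the outcome is a change from baseline, a stable difference in motivation would partly cancel. Neither point removes the selection: the exclusion acts before randomisation, attendance is observed after it, and adjustment is only considered for baseline imbalance.

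Several stronger readings are tempting but not supported:

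- **That no control can qualify.** Taken word for word, the parenthesis would empty the control arm. That leaves no comparison and is plainly not meant.
- **That every control is kept.** The requirements of a valid measurement and no important deviation apply to both arms, and a full list of deviations may stand in a document not shown. Such a list could not make selection on attendance two-sided, because controls have no sessions to attend.
- **That 80% of 8 sessions is an error.** It gives 7 or more without ambiguity. Stating it in sessions is an editorial courtesy.
- **That mechanism is otherwise neglected.** Section 2.8 already lists the relevant measures at baseline and 12 months. What fails is the purpose attached to the per-protocol analysis.

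**Conclusion.** The concern holds as a minor point about the choice and labelling of a secondary analysis. It is not an error in the main analysis. The rule that the article states compares self-selected attenders with controls not selected on attendance. Randomisation does not protect that comparison, and it cannot show mechanism. This follows from sections 2.1 and 2.9 alone and depends on no assumed number.

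The direction, towards benefit, is plausible but not demonstrated. The size is unknown. With assumed correlations of 0.2 to 0.3 it is about 0.10 to 0.15 SD at 70% adherence (type I error of this analysis about 9 to 13%) and about 0.04 to 0.06 SD at 90% adherence (about 6%).

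A reader might infer that the trial's conclusion on efficacy is at risk. The documents do not support that, because the conclusion rests on the intention-to-treat comparison.

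**What to change.** Estimate the effect of attendance with a complier-average causal effect (instrumental-variable) analysis in all randomised patients with a primary measurement. Use randomised arm as the instrument and sessions attended (0 to 8, with 0 in controls) as the exposure. In its simplest form the effect per session is the between-arm difference in mean change divided by the mean number of sessions attended in the intervention arm. Attendance enters only the denominator, so the comparison stays between the randomised arms. The main analysis is an unadjusted Student test, so no covariates need to be carried over.

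State the assumptions: each session adds the same amount (linear dose), and allocation affects the outcome only through sessions attended. If a threshold such as 7 of 8 is used instead, say that it assumes no effect of partial attendance; if partial attendance does help, the estimate is inflated.

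If the per-protocol comparison is kept, label it descriptive, apply the other deviation criteria to both arms, and delete the clause on mechanisms of action. Base mechanism on the between-arm comparison of the P0.1 response to CO2, the VE/VCO2 slope and STAI, which section 2.8 already schedules at baseline and 12 months without restriction to one arm. That comparison shows whether Sophrology moves the proposed intermediate steps. It is not by itself a mediation analysis.

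The cost is some wording, one extra model, a wider interval than the naive per-protocol one, and reliance on the instrumental-variable assumptions. No new data are needed, because the attendance rule already requires session counts.

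### Adjustment is tied to observed baseline imbalance, which leaves the choice of analysis open and forgoes precision that pre-specified covariates would give

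*Protocol article*

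**What the plan says.** All references are to the protocol article.

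- **Section 2.9, first paragraph.** "Our main analysis will be an intention-to-treat analysis, in which each randomised subject will be analysed in his/her treatment arm". The change in percent predicted VO2max from inclusion to 12 months "will be compared between the groups using a Student test". No covariate is named.
- **Section 2.9, second paragraph.** A secondary per-protocol analysis is described, restricted to patients with a valid primary measurement who attended at least 80% of the sessions. The next sentence reads: "In case of non-comparability of the groups on one of the baseline characteristics, an adjustment will be considered". It names no threshold, no candidate covariates and no model. It does not say which analysis it governs or what status an adjusted result would have.
- **Section 2.1.** Allocation is 1:1, minimised on centre and on age group (13–17 and 18–25 years). Controls receive no Sophrology during the 12 months.
- **Sections 2.6 and 2.7.** The primary outcome is the change in percent predicted VO2max between M0 and M12.

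**The concern.** The article is not silent on adjustment, which could have been left to the analysis plan. It makes observed imbalance the reason for adjusting. That causes three problems.

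1. **Covariates are selected on the wrong ground.** In a randomised comparison a covariate is worth including because it predicts the outcome. Here, a non-prognostic variable that differs by chance would prompt adjustment. Baseline percent predicted VO2max, which is a component of the change score, would not unless it happened to differ. Centre and age group are balanced by the allocation method, so the rule would almost never reach them.
2. **The choice of analysis stays open.** Adjustment is only to be considered, with no criterion, once the groups' baseline data have been seen. If it is made, there are two candidate results and no statement of which is primary. Participants know their arm, so the choice should not depend on discretion.
3. **Precision is given up.** If baseline VO2max predicts change, leaving it out costs power that could be had from data already collected.

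**Working it through.** **Inputs.** Section 2.6 gives a mean VO2max of 39.4 with SD 8.9 ml/kg/min, a 10% effect ("we hypothesized to observe a VO2_max_ increase of 10% in the Sophrology group"), 80% power, two-sided 5%, 78 per group before loss and 94 after. A 10% effect is 0.10 × 39.4 = 3.94 ml/kg/min. The documents give no SD of the change and no correlation between change and baseline. I therefore take 3.94/8.9 as the standardised effect on the change, and correlations r of -0.3 and -0.5, as assumptions. With equal SDs at both visits, r² = (1 − ρ)/2, where ρ is the correlation between M0 and M12. So r = -0.3 corresponds to ρ = 1 − 2(0.09) = 0.82, and r = -0.5 to ρ = 1 − 2(0.25) = 0.50.

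**Step 1: the plan's own figure.** n per group = 2(1.960 + 0.842)² × 8.9² / δ².
- With δ rounded to 4.0: 1243.4/16 = 77.7, so 78, as stated.
- With δ = 3.94: 1243.4/15.52 = 80.1, so 81.
- 78 × 1.20 = 93.6, so 94, as stated.

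I use 78 per group below.

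**Step 2: power of the Student test.** d = 3.94/8.9 = 0.443. Noncentrality = 0.443 × √(78/2) = 2.765. Power ≈ Φ(2.765 − 1.960) = 0.79 (0.784 from the t distribution).

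**Step 3: power of ANCOVA on baseline.** The residual SD shrinks by √(1 − r²).
- r = -0.3: 2.765/√0.91 = 2.898; Φ(0.938) = 0.83.
- r = -0.5: 2.765/√0.75 = 3.192; Φ(1.232) = 0.89.

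**Step 4: simulated power of the conditional rule.** 6,000 trials per setting, 78 per group, ten independent normal baseline variables (baseline VO2max, three others with coefficient 0.2, six unrelated). The rule adjusts for whatever differs at p < 0.05. That threshold is my assumption; the article has none.

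| Analysis | r = -0.3 | r = -0.5 |
|---|---|---|
| Student test | 0.783 | 0.780 |
| Adjust only if imbalanced | 0.781 | 0.788 |
| Pre-specified ANCOVA on baseline | 0.817 | 0.887 |

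The conditional rule recovers almost none of the gain.

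**Step 5: type I error.** Same set-up under no effect, with 5, 10 or 20 baseline variables and 8,000 trials per setting. The Monte Carlo standard error is √(0.05 × 0.95/8000) = 0.0024.

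| Analysis | Range over the six settings |
|---|---|
| Student test | 0.045–0.056 |
| Pre-specified ANCOVA on baseline | 0.047–0.051 |
| Conditional rule, strictly applied | 0.036–0.049 |
| Better of the two p-values | 0.050–0.063 |

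Setting by setting, taking the better p-value adds 0.003 to 0.008 to the Student test's rate. Within the trials where adjustment was triggered, it rejects in 0.061 to 0.096.

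**Step 6: cost in degrees of freedom.** Baseline (1), five centres (4) and two age groups (1) use 6. With 156 patients, 154 residual degrees of freedom become 148, which is negligible.

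**The case against.** **Scope.** The Student test is stated without condition as the main comparison, and the adjustment sentence comes directly after the per-protocol analysis. The attendance requirement in that analysis can act only on the Sophrology arm, so its baseline differences need not be due to chance, and adjusting for them is reasonable. This stands in part: a reader might infer that the sentence plainly governs the primary analysis, and the text does not establish that. Nor does it confine the sentence to the per-protocol set, and that ambiguity is part of the defect.

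**Error rate.** A reader might infer that the rule breaks the 5% level. The check does not support this. Strict use was at or below 5%, and deliberate choice of the better result inflates the overall rate only modestly.

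**Frequency.** A reader might also infer that chance imbalance would trigger adjustment in a large share of such trials. Any such rate needs a threshold and a set of independent characteristics. The article gives no threshold, its exercise-test measures are related to one another, and adjustment is only to be considered, so nothing is triggered automatically.

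**Baseline testing.** Section 2.9 summarises baseline by frequencies, means and standard deviations. It announces no significance tests, so there is nothing to correct there.

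**Validity and detail.** An unadjusted t test of a change score is valid under randomisation, and covariate lists are often left to an analysis plan. Both are true. The point is that the article states a data-dependent rule which such a plan would have to override, and that a better analysis is available from data already collected.

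**Conclusion.** The point holds as a worthwhile improvement to a badly fixed rule, not as an error that invalidates the primary test. The main harms are the open choice of analysis and the lost precision: power of about 0.78 under the Student test or the conditional rule, against about 0.82 to 0.89 with pre-specified ANCOVA on baseline.

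The size of the gain rests on the assumed correlations and on treating 3.94/8.9 as the standardised effect on the change. It shrinks towards nothing as the M0–M12 correlation approaches 1. Any further gain from centre and age group is not counted. The direction does not depend on these values: if baseline predicts change, pre-specified adjustment helps whatever the observed balance, and the conditional rule mostly does not.

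**What to change.** In section 2.9, replace the Student test and the adjustment sentence with the following, and carry it into the analysis plan:

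- The primary intention-to-treat analysis is an ANCOVA of M12 percent predicted VO2max on treatment arm, with baseline percent predicted VO2max, centre and age group as covariates whatever the observed balance. Using the change as the response gives the same treatment effect once baseline is in the model.
- Any other adjusted model, including adjustment for imbalance in the per-protocol set, is a sensitivity analysis with its covariates listed before database lock. It supplements the primary result and does not replace it.

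This costs two or three sentences, no new data and no increase in sample size.
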